### Sample size justification

Using CANTAB cognitive test responses already collected in the ISLAND Project (n = 3,000), we estimate that we will collect > 1,000 complete cases (TapTalk app completion twice in 18 months and CANTAB at baseline and 24 months), which is ample for logistic regression with a single fixed-effect predictor variable.

### AIM 3

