### Sample size justification

The precise combination of blood-based biomarkers used to determine ‘positive’ preclinical AD pathology is yet to be determined as the scientific literature is developing quickly and new biomarkers are being developed regularly. We will review the literature before deciding on the best biomarker test, or combination of tests, that should be used to define AD pathology risk most accurately.

Currently p-tau 181 is considered one of the most accurate blood-based biomarkers for preclinical AD risk and we have therefore based our sample size calculation on this biomarker. As new tests are developed and are likely to be even more sensitive/specific than p-tau 181, the current calculation is a conservative estimate. We estimate that 17% of cognitively normal adults within our cohort have p-tau 181 in the preclinical AD range [55]. There are no tests of DDK compared to AD biomarkers, so we have based all calculations on finger tapping data.

We have performed ROC curve analysis using open data from Mollica et al. to calculate sensitivity and specificity of finger tapping speed and variability to predict CSF p-tau 181 [20]. This showed area under ROC curve (AUC) of 0.75 for a null linear model including age, gender and years of education, but not finger tapping. We calculated that the sample size to compare a screening test with an AUC > 0.90 against the null model requires 60 preclinical AD cases (positive p-tau181) and 290 healthy ageing controls (negative p-tau181). Thus, we will use 350 in the development dataset (expected 60 [17%] preclinical AD cases) and 150 in the validation dataset (expected 25 [17%] preclinical AD cases) to test cut-offs from the development model. The PROBAST tool [56] for assessment of prediction and diagnostic method studies confirms these development and validation strategies have a low risk of bias.

### AIM 2

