#### Statistical analysis

The data from participants who complete TapTalk on two or more occasions over an 18-month period, and CANTAB on two occasions (2021 and 2023) will be included in the analysis. De-identified ISLAND Project participants will be classified as cognitively ‘stable’ or ‘declining’ using longitudinal CANTAB cognitive scores. TapTalk scores will be calculated using algorithms developed in Study 1. Logistic regression will be used to estimate the odds of a participant being confirmed as ‘declining’ at time T_2_ (24 months) conditioned on TapTalk score at time T_1_ (12 months). The overall outcome of Study 2 will be a smartphone app, TapTalk, that is usable, reliable and validated against established online CANTAB cognitive tests.

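### Study 2.3 validates TapTalk against cognitive decline with TapTalk score as the only predictor, so the planned odds ratio cannot show that TapTalk adds anything beyond age

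*Protocol article*

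**What the plan says.** Under Aim 2, Study 2.3, Statistical analysis, participants are "classified as cognitively ‘stable’ or ‘declining’ using longitudinal CANTAB cognitive scores". The model follows: "Logistic regression will be used to estimate the odds of a participant being confirmed as ‘declining’ at time T_2_ (24 months) conditioned on TapTalk score". The TapTalk score used is the 12-month one. On the predictor, "TapTalk scores will be calculated using algorithms developed in Study 1". No covariate is named.

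The Aim 2 Sample size justification starts from the roughly 3,000 people with CANTAB data, says "we estimate that we will collect > 1,000 complete cases", and judges that number as one "which is ample for logistic regression with a single fixed-effect predictor variable". It gives no proportion declining, odds ratio, significance level or power.

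Elsewhere the article treats demographics differently:
- The Statistical analysis sections of Aims 1 and 3 both list age, gender, APOE status, years of education and handedness as possible covariates.
- The Aim 1 Sample size justification takes a demographics-only model as the benchmark: "This showed area under ROC curve (AUC) of 0.75 for a null linear model including age, gender and years of education".
- The Background calls age the main non-modifiable risk factor for dementia.
- The Aim 1 inclusion criteria adjust CANTAB PAL errors for age. The Study 2.3 outcome carries no such statement.

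**The concern.** Study 2.3 is meant to deliver an app validated against CANTAB. A new screening test is useful to the extent that it tells us more than a person's age already does. Older people can be expected to tap and articulate more slowly and also to decline more. A score that merely tracks age would then be associated with decline. If age entered the Study 1 algorithm, the score would carry age by construction. One unadjusted odds ratio cannot tell these situations apart from a genuine TapTalk signal.

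Two smaller matters follow from the same sentences. Cutting a CANTAB change into two classes gives up part of the outcome information. And adequacy is judged on total sample size, whereas the precision of a logistic model depends on how many people are classed as declining.

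**Working it through.** **The plan's own figure.** The only arithmetic behind the sample size is a yield: 1,000/3,000 = 33%. Without a decline rate, effect size, significance level or power, it cannot be reproduced as a power calculation. The checks below therefore use stated assumptions.

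**1. Can age alone produce the association?** Simulation with n = 1,000, 500 runs per cell, two-sided 5% level and no direct TapTalk effect. Age is related to TapTalk (correlation r) and to decline (odds ratio per SD of age). Both values are assumptions; the article gives neither. Paired entries are for 10% and 20% declining.

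| r | Age OR per SD | Unadjusted TapTalk OR per SD | Significant, unadjusted | Significant, age added |
|---|---|---|---|---|
| 0.3 | 1.5 | 1.12 / 1.12 | 18.8% / 31.6% | 4.2% / 4.0% |
| 0.3 | 2.0 | 1.22 / 1.21 | 46.2% / 64.6% | 5.6% / 6.2% |
| 0.5 | 1.5 | 1.22 / 1.22 | 44.4% / 69.8% | 3.8% / 6.8% |
| 0.5 | 2.0 | 1.39 / 1.40 | 88.2% / 97.8% | 4.4% / 3.8% |

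With age in the model the TapTalk OR returns to about 1.00 in every row. The Monte Carlo standard error at a true 5% is √(0.05 × 0.95/500), about 1 percentage point, so the last column is compatible with 5%.

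Rough check by formula: log OR ≈ r × ln(age OR) and z ≈ log OR × √(n p(1−p)). For r = 0.3, age OR 1.5 and p = 0.10: 0.3 × 0.405 = 0.122, OR 1.13, z = 0.122 × √90 = 1.15, so about 21% significant. That is close to the simulated 18.8%.

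Controls: where TapTalk is unrelated to age, or decline is unrelated to age (as under effective age norming), the unadjusted rate is 3.8% to 7.0%.

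**2. Information kept by the split.** For a normally distributed change score and small effects, the fraction kept is φ(z_p)²/(p(1−p)), where p is the proportion declining.

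| Declining | Kept | Lost | Equivalent n out of 1,000 |
|---|---|---|---|
| 5% | 0.224 | 78% | 224 |
| 10% | 0.342 | 66% | 342 |
| 20% | 0.490 | 51% | 490 |
| 30% | 0.576 | 42% | 576 |
| 50% | 0.637 | 36% | 637 |

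The loss passes one half only below about 21% declining.

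**3. Precision at n = 1,000.** The detectable OR per SD is exp[(1.96 + 0.84)/√(1,000 p(1−p))], at 80% power and a two-sided 5% level (both assumed).
- p = 5%: exp(2.80/√47.5) = 1.50
- p = 10%: exp(2.80/√90) = 1.34
- p = 20%: exp(2.80/√160) = 1.25
- p = 50%: exp(2.80/√250) = 1.19

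If covariates explained 30% of TapTalk variance (assumed), the log OR is divided by √0.7. The detectable OR becomes 1.42 at 10% declining and 1.63 at 5%. For a six-parameter model, 10% declining gives 100/6 = 16.7 events per parameter and 5% gives 50/6 = 8.3.

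**The case against.** The strongest reply is that the article leaves open the facts on which the age argument turns. The declining label may be age-normed, as PAL is for Aim 1 eligibility, and the false-positive problem would then largely disappear. The score may already include demographics, so that adjusting for age again asks a different question. An unadjusted odds ratio is also a legitimate description of raw prediction. All of this stands, and it makes the point conditional. It does not remove it: the article states the single predictor outright, so this is not detail left to an analysis plan, and an age-containing score would make an unadjusted association less informative.

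A reader might infer several stronger claims that the document does not support:
- *That most CANTAB information is thrown away.* This needs fewer than about 21% declining, and no proportion is given.
- *That calling the sample ample is wrong.* It is unsupported by any stated decline rate or effect, but 1,000 people detect modest odds ratios and would usually allow adjustment.
- *That a significant result would be due to age.* The simulated rates rest on assumed associations and fall to the nominal level if either link is absent.
- *That the AUC of 0.75 shows demographics predict CANTAB decline.* It concerns CSF p-tau 181 in an outside dataset. It shows only that the plan itself regards demographics as the benchmark.
- *That baseline-adjusted linear regression must be the sole primary analysis.* Baseline CANTAB is measured with error. Suppose nobody truly changes, TapTalk correlates 0.2 with true baseline cognition, and CANTAB reliability is 0.7 (all assumed). The partial correlation is √0.7 × 0.2 × 0.3/√[(1 − 0.49)(1 − 0.028)] = 0.071. With n = 1,000 that gives z of about 2.25 and a significant result in about 62% of studies. At reliability 0.9 the figure is about 29%.

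**Conclusion.** The point holds in a conditional form. Study 2.3 fixes an analysis with TapTalk as the only predictor of decline, out of line with the covariates contemplated in Aims 1 and 3 and with the demographics-only null model in Aim 1. Unless the declining label is effectively age-normed, that analysis cannot show information beyond age. Under the assumed range in the first table, the unadjusted test is significant in about 19% to 98% of studies with no direct TapTalk effect, and in about 4% to 7% with age added.

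The split is a secondary weakness, with a loss of 36% or more depending on a decline rate the article does not give. The sample-size sentence is incomplete rather than shown to be false. The matter should be corrected before analysis, but it does not undermine the data collection.

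**What to change.** - Report the TapTalk association both unadjusted and adjusted for age, gender and years of education, or report the gain over a demographics-only model, as Aim 1 does.
- State whether the TapTalk score already contains any of these variables.
- Define the declining label and say whether it is age-normed.
- Alongside the stable/declining logistic model, add an analysis of CANTAB as a continuous score with the same covariates. If it adjusts for baseline CANTAB, note that measurement error in baseline can leave residual confounding, and give the change-score result as a sensitivity analysis.
- Rewrite the sample-size statement around the expected number of decliners and the odds ratio detectable with that number.

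Cost: wording and analysis time. ISLAND already holds the demographic and CANTAB data, so nothing new need be collected. The adjusted TapTalk effect may be smaller and slightly less precise, and if only about 5% decline, the number of covariates would have to be kept small.

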#### Design

We will undertake a prospective study of 200 adults who *have cognitive symptoms* to validate TapTalk against gold-standard clinical consensus diagnosis of MCI and AD dementia. Secondary aims include determining the usability of TapTalk in a cohort with cognitive symptoms and comparing the usability and validity of TapTalk with commonly used brief screening tools. The study will be undertaken at two sites – the Royal Hobart Hospital (RHH) and the University of Tasmania ISLAND Cognitive Clinic with 100 people recruited from each site; see Fig. 5 for an overview of the study design.

The *inclusion criteria* are adults aged ≥ 50 years old with at least 3 months of persistent cognitive symptoms (patient- or family-reported).

The *exclusion criteria* are any adults who are < 50 years old, acutely unwell, have significant impairment of hand function or speech function, lack capacity to consent to the research study, or already have a known diagnosis of MCI or dementia.

**Fig. 5 Fig5:**

Prospective evaluation of usability and validity of TapTalk smartphone application (n = 200)

### Recruitment from the hospital

There are several steps to recruiting eligible participants to the study and these are necessary as we will recruit from a pool of patients who are moving through their medical care at the RHH. Clinicians working at RHH (JA, NF, AB) will oversee the identification of 100 patients from the acute medical/subacute sites who may be eligible for the study. We will assess capacity to consent in line with standards of Good Clinic Practice research governance. Specifically, we will check that the participant has understood the information provided on the study, that they can retain it and can recount the key parts back to the researcher, that they can weigh up the information and that they can freely decide to participate.

After obtaining written consent, a research assistant (RA) will collect demographic and clinical details on the Data Collection Form (see supplementary files). The RA will ask the participant to complete the TapTalk assessment using the study smartphone; participants will be invited to hold the phone themselves, or to prop it up on a table, and to complete the TapTalk assessments without the RA prompting them (as it is designed as a ‘self-test’). The duration of testing is expected to take about 2–3 min. If the participant prefers the RA to help them, the RA will hold the smartphone and/or help guide participants through the tests as requested. They will make a note in the Data Collection Form (see supplementary files) how much help was administered and the indications for this, as this is valuable information for the research team to evaluate when considering usability of TapTalk in clinical cohorts.

The RA will then administer the MoCA, a standardised brief cognitive screening test that is commonly used in clinical practice and typically takes about 10–15 min to complete [59, 60]. The addition of this established cognitive test will allow for validation of the TapTalk scores, as well as comparison of the two tests (established cognitive test vs. TapTalk) compared to the clinical diagnosis (see later, ISLAND Clinic consensus diagnosis section). The MoCA outperforms the long-established MMSE in screening for cognitive impairment [60]. However, recent data suggest cultural differences may affect performance. Should the MoCA score suggest cognitive impairment for participants from culturally and linguistically diverse backgrounds or First Nations people, additional screening will be completed using the Rowland Universal Dementia Assessment Scale (RUDAS) [61].

After the participant has completed TapTalk and the cognitive test(s), the RA will ask the participant to complete a self-report ‘User Experience Questionnaire’ (see supplementary files). If the participant prefers the RA to read the questions out to them, the RA will do so and make a note of this in the Data Collection Form. This will provide valuable information on usability of TapTalk in a clinical cohort in comparison to a standard cognitive test.

After completing the test protocol, the RA will give the participant an information leaflet on the ISLAND Clinic (https://islandclinic.utas.edu.au/) that they can pass on to their GP if they would like to have further cognitive assessments. This GP letter will include a numerical research code used during the TapTalk assessments so that, if the participant attends the clinic, their data can easily be linked. The ISLAND Clinic protocol has been described previously in Alty et al. [62]; in brief it is a state-wide cognitive clinic that provides facilities and expertise for clinical diagnosis in a ‘one-stop’ interdisciplinary model where participants will have cognitive, medical and movement assessments performed on one day. They will also have an MRI brain scan, blood tests and an array of other tests. The interdisciplinary team formulates a consensus diagnosis for each participant attending the clinic. One of the clinicians on the team delivers the diagnosis to the participant on the same day and provides a detailed management plan for the participant and GP. The Clinic is supported by research funding and is Medicare bulk-billed for participants with no out-of-pocket costs.

This means that through the standard ISLAND Clinic processes, all participants recruited through the RHH will have the opportunity to have thorough medical and cognitive assessments, including neuropsychological tests, an interdisciplinary consensus diagnosis and management plan for their cognitive symptoms [62]. The established diagnosis of ‘cognitively unimpaired’ (objectively ‘normal’ on ISLAND Clinic tests), ‘MCI’ and ‘AD dementia’ (AD and mixed AD/vascular) also allow us to validate TapTalk scores against the gold standard clinical diagnosis.

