### Statistical analysis

We will calculate AUC for TapTalk and MoCA (or RUDAS) to predict clinical diagnosis of MCI and AD dementia (defined as AD or mixed AD/vascular); 95% confidence intervals will be obtained using bootstrapping. Covariates may include age, gender, APOE4, years of education, and handedness. We will estimate cut-off scores for TapTalk and MoCA (or RUDAS) to differentiate between cognitively unimpaired vs. MCI, and between cognitively unimpaired vs. AD using the Youden index to optimise the trade-off between sensitivity and specificity. Classification accuracy (sensitivity and specificity) using these cut-offs will be compared using McNemar’s test. Participants diagnosed with other types of dementia (such as Dementia with Lewy Bodies or Frontotemporal Dementia) will not be included in this analysis.

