### Sample size justification

As the conditional dependence between TapTalk and MoCA (or RUDAS) is unknown, the nominal power of the study cannot be calculated. However, Roalf et al. compared the diagnostic accuracy of MoCA with MMSE using a comparable sample size (n = 126 MCI and n = 140 healthy controls) and found a significant difference (in favour of MoCA) between the two diagnostic tests [63].

The main outcome of Study 3 will be an externally validated TapTalk smartphone test with determined precision for prospectively predicting risk of MCI and AD in adults ≥ 50 years old with cognitive symptoms. Secondly, we will have a measure of the accuracy and usability of the TapTalk smartphone test compared to MoCA in adults ≥ 50 years old with cognitive symptoms.

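### Aim 3's 200 participants are not comparable to the cited 266: three diagnoses share them, and hospital recruits get the reference diagnosis only if they choose to attend the clinic

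*Protocol article*

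**What the plan says.** The Design section of Aim 3 states: "We will undertake a prospective study of 200 adults who" have cognitive symptoms, "with 100 people recruited from each site". The sites are the hospital and the ISLAND Cognitive Clinic.

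Under Recruitment from the hospital, recruits complete TapTalk and the MoCA and then receive a leaflet "that they can pass on to their GP if they would like to have further cognitive assessments". The accompanying letter carries a research code so that, "if the participant attends the clinic, their data can easily be linked". The diagnosis comes from the clinic: "The interdisciplinary team formulates a consensus diagnosis for each participant attending the clinic". The same section says that all hospital recruits will have the opportunity of this work-up; it does not make the visit a study procedure. The section on GP referrals adds that hospital recruits seen at the clinic also consent there to the use of their clinic data.

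The Statistical analysis section of Aim 3 states: "We will calculate AUC for TapTalk and MoCA (or RUDAS) to predict clinical diagnosis of MCI and AD dementia". It then derives Youden cut-offs for unimpaired versus MCI and for unimpaired versus AD, and compares the two tests by McNemar's test. Participants with other types of dementia "will not be included in this analysis".

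The Sample size justification of Aim 3 says that nominal power cannot be calculated. Its only support is a cited study that "compared the diagnostic accuracy of MoCA with MMSE using a comparable sample size" of 126 people with MCI and 140 healthy controls.

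**The concern.** The number recruited and the number that can enter the accuracy analysis are different quantities, and the size justification uses only the first. A hospital recruit without a consensus diagnosis adds nothing to an AUC, a cut-off or McNemar's test against that diagnosis. Those who have one are the 100 clinic recruits plus the hospital recruits who decided to go through their GP, attended and consented to data access.

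Two things are at stake. The first is precision. The main outcome of Study 3 is a test with determined precision, and the only argument for its size is likeness to a study with more people in fewer groups. The second is possible bias. If the decision to attend is related to how people performed, or to how severe their condition is within a diagnosis, the verified hospital participants misrepresent the sensitivity and specificity of both tests in the hospital population.

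**Working it through.** **Inputs from the protocol.** 100 hospital and 100 clinic recruits; 126 MCI and 140 controls in the cited study; three diagnostic groups and two contrasts.

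**Assumed inputs, none given in the protocol.** Clinic attendance q among hospital recruits, 30–70%, with 100% as the ceiling. Share with other dementias o, 5–20%. Case mix (unimpaired/MCI/AD): one third each, 20/45/35 and 30/40/30.

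**The plan's own figure.** 100 + 100 = 200. The benchmark is 126 + 140 = 266, and 200/266 = 75%. The plan is smaller before any loss.

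**Usable number** = (100 + 100q) × (1 − o).
- Full attendance: 200 × 0.80 = 160 to 200 × 0.95 = 190.
- 30–70% attendance: 130 × 0.80 = 104 to 170 × 0.95 = 161.5.

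**Number per contrast** = usable number × share in the two groups compared. The smallest share is 0.20 + 0.35 = 0.55 (unimpaired versus AD). The largest is 0.30 + 0.40 = 0.70 (unimpaired versus MCI).

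| Attendance | Lowest | Highest | Share of 266 |
|---|---|---|---|
| 100% | 160 × 0.55 = 88 | 190 × 0.70 = 133 | 33–50% |
| 30–70% | 104 × 0.55 = 57 | 161.5 × 0.70 = 113 | about 21–42% |

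**Where the shortfall comes from.** As multipliers on 266: smaller total 0.75; other dementias 0.80–0.95; three-way split 0.55–0.70; optional attendance 130/200 = 0.65 to 170/200 = 0.85. The split is the largest. The first three alone bring 266 down to 88–133.

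**Precision.** The Hanley–McNeil 95% half-width for n1 cases and n0 controls is 1.96 × √{[A(1−A) + (n1−1)(Q1−A²) + (n0−1)(Q2−A²)]/(n1·n0)}, with Q1 = A/(2−A) and Q2 = 2A²/(1+A). At an assumed A = 0.80, Q1 − A² = 0.0267 and Q2 − A² = 0.0711.
- Cited study (126 and 140): √(13.378/17640) × 1.96 = 0.054.
- Full attendance, largest contrast (76 MCI and 57 unimpaired): √(6.142/4332) × 1.96 = 0.074.
- Full attendance, smallest contrast (56 AD and 32 unimpaired): √(3.831/1792) × 1.96 = 0.091.
- 30–70% attendance, by the same formula: 0.080 (64.6 and 48.45) to 0.113 (36.4 and 20.8).

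**Possible bias, as an illustration.** Take true sensitivity 0.72 and specificity 0.73 in both arms at a fixed cut-off. Assume 70% of test-positive and 30% of test-negative hospital recruits attend, and the equal-sized clinic arm is fully verified.
- Hospital arm, sensitivity: 0.72 × 0.7 / (0.72 × 0.7 + 0.28 × 0.3) = 0.504/0.588 = 0.86.
- Hospital arm, specificity: 0.73 × 0.3 / (0.73 × 0.3 + 0.27 × 0.7) = 0.219/0.408 = 0.54.
- Pooled sensitivity: (0.72 + 0.504)/(1 + 0.588) = 0.77.
- Pooled specificity: (0.73 + 0.219)/(1 + 0.408) = 0.67.

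Reversing the attendance rates reverses the direction. With equal rates, both values return to 0.72 and 0.73.

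**The case against.** A reader might infer that the accuracy results will be biased because verification depends on the test result. The protocol does not support that. Nowhere does it say that TapTalk or MoCA scores are given to the participant or the GP; the letter is described as carrying a research code. If attendance depends on the diagnosis alone, sensitivity and specificity are unbiased and only the case mix shifts. If it depends on neither test result nor diagnosis, only numbers fall. The illustration also uses a fixed cut-off, whereas the plan estimates its cut-offs from the verified data, and it says nothing about the AUC or the comparison between tests. What stands is that selection on performance, or on severity within a diagnosis, is plausible in a voluntary pathway and cannot be excluded.

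A reader might also infer that non-attendance is what makes the size claim fail. It is not: the claim fails at full attendance. Attendance above 70% is possible, since the clinic is state-wide, takes one day and has no out-of-pocket cost. That moves the numbers towards 88–133, not to 266. Even pooling MCI and AD into one contrast would give at most 200.

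Three further points are fair. The comparison is offered as precedent, with an open admission that power cannot be calculated. Unverified recruits still serve the usability aim and the comparison of TapTalk with the MoCA. And the handling of missing diagnoses may sit in an analysis plan not shown, so its absence here is not the finding. None of this repairs the comparability statement, which the protocol itself makes.

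**Conclusion.** The point holds. Aim 3's accuracy analysis rests on 100 clinic recruits plus self-selected hospital attenders, less other dementias, spread over three diagnoses. Each contrast would have about one third to one half of the cited 266 at full attendance, and about one fifth to two fifths at 30–70% attendance. At an AUC of 0.80 the interval half-width would be about 0.074–0.091 and 0.080–0.113 respectively, against 0.054 for the cited study. These ranges depend on the assumed attendance, case mix, other-dementia share and AUC. That the plan falls short of 266 does not: 200 is already the ceiling.

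Bias in sensitivity and specificity is a conditional risk. The shift from 0.72/0.73 to 0.77/0.67 shows what one assumed attendance pattern would do; it is not a prediction.

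**What to change.** 1. In the Sample size justification of Aim 3, replace the comparability statement with the expected verified numbers per contrast over a range of attendance. Give the AUC interval width these produce, or McNemar power over a range of discordance.
2. In the Statistical analysis of Aim 3, report clinic attendance among hospital recruits by TapTalk and MoCA score. Estimate AUC, sensitivity and specificity with a verification-bias correction. This can be inverse-probability weighting of the verified hospital participants, or multiple imputation of the diagnosis with other dementia as one of its categories, so that the planned exclusion still works. Use TapTalk, MoCA, age, gender and Data Collection Form items, which are collected at the hospital before any clinic visit. State the assumption that these variables explain attendance, and add a sensitivity analysis for departures from it.
3. Report results by recruitment source. The GP-referred arm is fully verified but is a different population from hospital patients, so it cannot stand in as the reference result for them.

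The cost is a few paragraphs of text, slightly wider intervals and a less favourable stated size. No additional data collection is needed.
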